### Measures

#### The Proportion of Studies Completed

The primary outcome of interest is the proportion of studies completed. A study is considered complete if a participant reaches the end of a trial without a study failure (involuntary withdrawal) or voluntary withdrawal. A study failure occurs when there is insufficient data generated during baseline or any treatment period due to missed treatments (self-reported) or incomplete assessments. Participants must complete all assigned treatment and assessment tasks for 1/3 of the days in each period to avoid study failure and involuntary withdrawal, except for the 5-day study where all tasks must be completed each day because there is only one day per period. For the 15-day and 27-day trials, we inevitably expect participants to miss some tasks during these periods, so we wanted to allow for some nonadherence. While the requirement of task completion for 1/3 of the days in each treatment period is somewhat arbitrary, the choice of 1/3 of the days means that, at a minimum, completed 15-day trials will at least have the same amount of data as completed 5-day trials and are also likely to have more. We applied the same criteria to the 27-day trial so that the criteria for study failure are uniform across all three study durations. It is also worth noting that the 3 study lengths are primarily dictated by our randomized, counterbalanced, crossover design that defines N-of-1 trials: NABBA or NBAAB, where N is baseline, A is treatment period A, B is treatment period B, and AB or BA is a block. The minimum N-of-1 trial for a counterbalanced design with two blocks is five days if you have only one day per treatment period and one day of baseline.

We anticipate that a 27-day trial approaches what is likely to be the maximum number of days we could expect people to participate with reasonable adherence for this study, which requires daily tasks. The 15-day trial splits the difference between these two extremes. Put another way, we chose to vary treatment period lengths by one day for the 5-day trial, three days for the 15-day trial, and five days for the 27-day trial. We could have selected a different design, such as treatment periods that are 1, 2 and 3 days long rather than 1, 3 and 5 days long for each group; however, to evaluate the impact of study durations and notification levels on completion rates, we reasoned it would be better to have a more extensive spread across the three groups.

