#### Exploratory Analyses

We will also use descriptive statistics to summarize measures collected in the Brain Boost Study. We will compare the proportion of studies completed and trial adherence across the six groups of participants (three study durations and two notification levels), removing from this analysis anyone that turned off notifications. We will also compare the proportion of completed trials that are deemed by the N1 app to demonstrate a meaningful difference in treatment response on any of the cognitive tests, across the three study durations.

We also want to learn about the factors that influence the measure of trial adherence to improve future study designs. We will use Bayesian methods for exploratory analysis to get a baseline for future analyses, which we expect will also use Bayesian methods of analysis. The exploratory analysis will utilize a Bayesian survival-style model with semicompeting risks throughout the study. It will be assumed that a participant is in the study up until the time of study completion, voluntary withdrawal, or involuntary withdrawal (ie, study failure). Daily adherence will be assessed among all participants in the study on a given study day. There will be two types of events considered: (1) daily nonadherence, as a nonterminal repeating event; and (2) early withdrawal (including both voluntary withdrawal and involuntary withdrawal due to study failure) as a terminal (nonrepeating) event. The daily rate of nonadherence and early withdrawal will be modeled as a Poisson process with the rates impacted by several covariates, including study day (number of days since the start of the study, estimated with a random walk prior), notification level (light versus moderate); self-reported motivation level (5-point ordinal scale), day of the week (if distinguishable from study day), and subject-specific shared frailty term.

The cumulative probability of early withdrawal can be used to estimate the inverse probability of study completion. Also, the daily rates of adherence can be used to improve study design for future participants, depending on self-reported motivation and subject-specific characteristics. As in the primary analysis of the study completion rate, we will additionally adjust this analysis of adherence for age and sex.

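### The exploratory model pools rule-based study failure with voluntary withdrawal and calls nonadherence nonterminal, so without study duration its withdrawal curve can badly misstate 5-day completion

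*Protocol article*

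**What the plan says.** The protocol article, under Exploratory Analyses, names two event types. The first is "daily nonadherence, as a nonterminal repeating event". The second is "early withdrawal (including both voluntary withdrawal and involuntary withdrawal due to study failure) as a terminal (nonrepeating) event". On the model it states: "The daily rate of nonadherence and early withdrawal will be modeled as a Poisson process with the rates impacted by several covariates". The listed covariates are study day with a random-walk prior, notification level, motivation, day of the week and a "subject-specific shared frailty term", with later adjustment for age and sex. Study duration, treatment period and misses so far are not on the list. The cumulative withdrawal probability is then to be turned into a probability of study completion.

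The section The Proportion of Studies Completed defines failure by rule: "A study failure occurs when there is insufficient data generated during baseline or any treatment period due to missed treatments (self-reported) or incomplete assessments". The threshold is: "Participants must complete all assigned treatment and assessment tasks for 1/3 of the days in each period to avoid study failure", "except for the 5-day study where all tasks must be completed each day because there is only one day per period". The Adherence section defines a day as adherent when both the treatment and the assessment were adhered to. These are the tasks that the failure rule counts.

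**The concern.** The two event types are presented as separate processes joined by a participant-level frailty. Part of the second is a deterministic function of the first, and the function changes with randomized duration: one miss ends a 5-day trial, while a 15- or 27-day trial tolerates several misses per period. A frailty describes how participants differ from one another. It does not describe a within-person threshold.

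With no duration term, participants with the same covariates receive the same withdrawal curve over study days whichever arm they are in. The completion probability read from it at day 5 is then dominated by the longer arms, which supply 80% of participants and in which a single miss has no such consequence. At stake is the completion estimate that the article says can be taken from this curve, and the interpretation of the withdrawal rate as participant behaviour.

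**Working it through.** **1. The rule reproduces Table 2.** Treatment periods last 1, 3 and 5 days. The 27-day baseline is inferred as 27 − 4×5 = 7 days; the other baselines equal one treatment period. Minimum actions = 2 × the sum over periods of (period length ÷ 3, rounded up):
- 5-day: 2 × (5×1) = 10
- 15-day: 2 × (5×1) = 10
- 27-day: 2 × (3 + 4×2) = 22

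These equal the 10, 10 and 22 in Table 2, so this reading of the rule is the article's own.

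**2. Misses that force failure.** Period length − minimum adherent days + 1:
- 5-day: 1 − 1 + 1 = 1
- 15-day: 3 − 1 + 1 = 3
- 27-day: 5 − 2 + 1 = 4 in a treatment period, 7 − 3 + 1 = 5 in baseline

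In the 5-day arm every nonadherent day meets the failure criterion.

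**3. Failure from the rule alone.** Assume a daily miss probability q, the same in every arm, independent days and no voluntary withdrawal. Restrict to participants who began (at least one adherent baseline day). Then P(failure) is:
- 5-day: 1 − (1−q)^4
- 15-day: 1 − (1−q³)^4, since one adherent day already satisfies its baseline
- 27-day: 1 − [P(at least 3 of 7 adherent) ÷ (1−q⁷)] × P(at least 2 of 5 adherent)^4

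| q | 5-day | 15-day | 27-day |
|---|---|---|---|
| 5% | 18.6% | 0.05% | 0.01% |
| 10% | 34.4% | 0.4% | 0.2% |
| 20% | 59.0% | 3.2% | 3.1% |
| 30% | 76.0% | 10.4% | 14.3% |
| 50% | 93.8% | 41.4% | 66.0% |

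Behaviour is identical along each row, so the differences between arms come from the rule and the period lengths.

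**4. Effect on the day-5 completion estimate.** The article gives no daily rates, so two pairs are assumed. Table 3 gives 128, 384 and 128 beginners, that is 20/60/20. Until the end of day 5 participants leave only through early withdrawal, so the pooled curve at day 5 is the weighted mean of the arm-specific probabilities of still being in the study. By hand, take day 1 as event-free, let withdrawal precede each day's tasks, and ignore the very rare failures in the longer arms before day 6.

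*20% misses, 8% withdrawal:*
- 5-day arm: (0.92 × 0.80)^4 = 0.736^4 = 0.293
- Longer arms: 0.92^4 = 0.716
- Pooled: 0.2 × 0.293 + 0.8 × 0.716 = 0.632

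*10% misses, 5% withdrawal:*
- 5-day arm: (0.95 × 0.90)^4 = 0.855^4 = 0.534
- Longer arms: 0.95^4 = 0.815
- Pooled: 0.2 × 0.534 + 0.8 × 0.815 = 0.759

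Simulation with the full rule and the beginner definition gives about 65% predicted against 30% true (64% to 66% across runs) and about 77% against 53%. It lies slightly above the hand figures because a longer-arm beginner whose first adherent day comes after day 1 cannot have withdrawn before it.

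The ordering convention matters little. If withdrawal follows each day's tasks, day 1 included, the first case becomes 0.92^5 × 0.80^4 = 0.270 true, against 0.2 × 0.270 + 0.8 × 0.659 = 0.581 pooled.

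**5. Share of early withdrawals that are failures.** In the 5-day arm in the first case, the daily failure probability is 0.92 × 0.20 = 0.184 and the daily withdrawal probability is 0.08, so failures are 0.184 ÷ 0.264 = 70%. In the same simulation they are about 2% (15-day) and 1% (27-day).

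**The case against.** Several points on the other side stand.

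- **Pooling matches the definition of completion.** A trial is complete only if it ends with neither failure nor voluntary withdrawal, so a curve meant to yield completion must account for both. The difficulty is treating both as one rate common to all durations.
- **The covariate list is open-ended and the article is condensed.** A duration term may exist in a fuller plan, and adding one would largely repair the day-5 misprediction. It would not repair the description of nonadherence as nonterminal and repeating in the 5-day arm, which the article states outright.
- **The label suits the longer arms**, with 80% of participants. At 20% independent misses or fewer, the rule alone ends only about 3% of those trials.
- **The model is exploratory.** The primary logistic regression on completion does not use it.

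Some stronger readings are tempting but unsupported:

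- A reader might infer that the withdrawal rate reflects the failure rule and not behaviour. It also contains voluntary withdrawal, and failure is itself missed-task behaviour passed through a threshold.
- A reader might infer that failure can fall only on certain days, or that a 5-day participant can have at most one recorded miss. The article does not say when failure is declared, and it lets participants record missed treatments at the end of the trial. The beginner definition also removes some baseline failures.
- A reader might infer that the analysis cannot inform future designs. The article gives that role to the daily adherence rates, not to the withdrawal curve.

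**Conclusion.** The point holds for the exploratory model. Study failure is a duration-specific function of the nonadherence that is modelled beside it, and in the 5-day study the nonterminal, repeating label contradicts the completion rule. Built on the listed covariates, the cumulative withdrawal curve can overstate 5-day completion by about 35 percentage points (65% against 30%) or 24 points (77% against 53%) under the two assumed behaviours.

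These sizes rest on assumed daily rates, independent days, equal behaviour across arms, beginners only and a 20/60/20 split. They describe a rate pooled by study day, not a full Bayesian fit with frailty. In the 15- and 27-day arms the contamination is small at modest independent miss rates and becomes material only when misses are frequent or clustered.

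**What to change.** Model voluntary withdrawal as the terminal event and daily adherence as the repeating outcome. In the 5-day arm, end follow-up for nonadherence at the first missed day. Take study failure out of the withdrawal rate. Derive failure, and hence completion, by applying the article's existing rule to the predicted daily adherence sequence in each arm, together with predicted voluntary withdrawal.

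At the least, treat voluntary withdrawal and study failure as separate terminal causes and include study duration in the model.

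The cost is revised analysis wording, a little more code for the prediction step and fewer terminal events to estimate from. Dates of adherence, nonadherence and early withdrawal are already collected, and the article already distinguishes the two kinds of withdrawal, so trial conduct does not change.

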#### Adherence

Treatment adherence is recorded as true for days when a participant completes a cognitive assessment and does not report treatment nonadherence. A participant is instructed to report any treatment nonadherence (eg, a missed treatment or the use of caffeine on a baseline day) in the app during the trial. At the end of the trial, participants are prompted to review a summary of their treatment adherence and may, if necessary, record missed treatments at this time as well. Assessment adherence is recorded as true when a participant completes all three cognitive tests in a daily cognitive assessment according to the user-specified schedule. Otherwise, assessment nonadherence is recorded (for both incomplete assessments and assessments that were not started). Daily adherence is recorded as true when a participant achieves both treatment adherence and assessment adherence for a given day during the trial.

We will also measure trial adherence, which is defined as the proportion of total actions completed by a participant during a trial. Here total actions are defined as the number of requested treatment actions (to take a treatment or abstain from all treatments) plus the number of requested assessment actions (take a cognitive assessment) during a trial. During the baseline period, participants take two actions per day in the form of abstaining from treatments and completing one cognitive assessment. During a treatment period, participants take two actions per day in the form of taking one treatment plus completing one cognitive assessment. The total number of actions requested, and the minimum number of actions required for each study duration are outlined in Table 2.

**Table 2 table2:** Total number of actions requested, and the minimum number of actions required for each study duration.

Study duration	Total number of actions requested	Minimum number of actions required to avoid study failure
5-day study	10	10
15-day study	30	10
27-day study	54	22

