We anticipate that most participants will schedule their treatments at the beginning of the day since caffeine consumption is a typical morning ritual. This represents two challenges for participant engagement that may not be generalizable across other N-of-1 trials. First, a recent survey of eight app-based digital health studies observed the highest levels of engagement in the evening [14]. Second, the act of abstaining from caffeine consumption for the duration of the baseline period may be perceived as a significant challenge for some individuals in a manner that may be altogether absent were we to be running a trial that compares two treatments of a different nature.

The estimation of completion rates in the total enrolled population for each study duration is a challenge because it not only depends on factors being evaluated in this study but also on recruitment and user characteristics that are uncontrolled outside of very permissive inclusion/exclusion criteria that focus on the safety of caffeine consumption. The novelty of app-based research, for example, may attract people that are more curious about the app or methods than they are committed to learning their results, which is why we included the question about motivation level as an exploratory measure. For example, one recent app-based research study on asthma experienced very high initial recruitment followed by rapid attrition and a small number of highly engaged participants [17]. The relationship between intrinsic motivation and treatment adherence has been examined elsewhere, such as long-term antiretrovirals for HIV/AIDS, weight loss, and various public health initiatives that involve behavior change [18].

One limitation of the collection of only minimal demographic information is that we will not be able to determine if the enrolled study population is representative of the general population outside of age and sex, which will limit the generalizability of our results. The most extensive study to date on retention in digital health studies showed a relationship between age and retention, with older populations having higher retention than younger participants [14]. They observed no relationship between sex and retention [14].

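### The exploratory adherence model pools three schedules on one study-day curve and names no baseline-period term, so any effect of caffeine abstinence could be misread as a time trend

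*Protocol article*

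**What the plan says.** The Exploratory Analyses section describes a survival-style model with two event types: daily nonadherence, which can recur, and early withdrawal, which ends follow-up. Both follow a Poisson process with "rates impacted by several covariates, including study day (number of days since the start of the study, estimated with a random walk prior". The other terms named are "notification level (light versus moderate); self-reported motivation level (5-point ordinal scale), day of the week" (if distinguishable from study day) and a subject-specific frailty. The section ends by saying that "we will additionally adjust this analysis of adherence for age and sex". The three durations are pooled: "Daily adherence will be assessed among all participants in the study on a given study day".

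The Adherence section sets a different task by period. At baseline, "During the baseline period, participants take two actions per day in the form of abstaining from treatments and completing one cognitive assessment". Later, "During a treatment period, participants take two actions per day in the form of taking one treatment plus completing one cognitive assessment". Failing either part makes the day nonadherent: "Daily adherence is recorded as true when a participant achieves both treatment adherence and assessment adherence for a given day during the trial".

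Strengths and Limitations says that "the act of abstaining from caffeine consumption for the duration of the baseline period may be perceived as a significant challenge for some individuals", and that this may not carry over to other N-of-1 trials.

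**The concern.** Study day is the only listed covariate that can follow the schedule. Notification level, motivation, frailty, age and sex are fixed within a person, and day of week does not track the period. Yet the same study day means different tasks in different arms. On day 3, for example, the 5-day participants are on treatment while the others are still abstaining from caffeine.

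If abstaining changes the chance of a nonadherent day, the study-day curve is the only place in the listed model where that within-person change can go. The curve would then mix two things: how adherence changes with time in a study, and how hard the caffeine-free baseline is. The withdrawal rate is exposed in the same way, because study failure is judged within each period.

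This matters because the section intends the daily rates to guide the design of future studies and to serve as a starting point for later analyses. A designer whose trial has no abstinence baseline would want the first component without the second.

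**Working it through.** **Inputs.** From The Proportion of Studies Completed: one baseline period, then four treatment periods of 1, 3 or 5 days in studies of 5, 15 or 27 days; tasks must be completed on one third of the days in each period (every day in the 5-day study). From Randomization: allocation 20/60/20. From Table 2: minimum actions 10, 10 and 22.

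**Baseline length.** Duration minus four treatment periods:
- 5 − 4×1 = 1 day
- 15 − 4×3 = 3 days
- 27 − 4×5 = 7 days

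**Check against Table 2.** With two actions per day, the minimum is 2 × (⌈baseline/3⌉ + 4 × ⌈treatment period/3⌉):
- 5-day: 2 × (1 + 4×1) = 10
- 15-day: 2 × (1 + 4×1) = 10
- 27-day: 2 × (3 + 4×2) = 22

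All three figures are reproduced. A 27-day split of 3 + 4×6 would give 2 × (1 + 4×2) = 18, so the 7-day baseline is the one the protocol uses.

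**Share of in-study participants who are abstaining (no withdrawal).**
- Day 1: 100%
- Days 2–3: 60 + 20 = 80%
- Days 4–5: 20%
- Days 6–7: 20/(60 + 20) = 25%, because the 5-day study has ended
- Day 8 on: 0%

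**Pooled study-day curve.** The documents give no abstinence effect, so the rates here are assumptions: 20% on every treatment day, 20%, 30% or 40% on every abstinence day, and no true time trend. Pooled rate = 20% + abstaining share × (abstinence rate − 20%).

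| Abstinence-day rate | Day 1 | Days 2–3 | Days 4–5 | Days 6–7 | Day 8 on |
|---|---|---|---|---|---|
| 20% (no effect) | 20% | 20% | 20% | 20% | 20% |
| 30% | 30% | 28% | 22% | 22.5% | 20% |
| 40% | 40% | 36% | 24% | 25% | 20% |

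A Poisson regression with a free effect for each study day (a random walk without smoothing) returns the same curves. Daily withdrawal of 10% leaves them unchanged.

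**Would a study-duration term be enough?** No. At a rate ratio of 1.5 (30% versus 20%), adding duration gives 0.302, 0.282, 0.222, 0.218 and 0.194. Adding a baseline-versus-treatment indicator instead gives a flat 0.20 and returns the ratio of 1.5. The two effects can be separated because, on days 2–7, the arms share study days but not tasks. With 128/384/128 participants and no frailty, the standard error of the log rate ratio is between 0.081 and 0.128 in this case, against log 1.5 = 0.41.

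**If only participants who begin are modelled.** The Primary Analysis section requires at least one fully adherent baseline day. With abstinence rate p and baseline of b days, the fraction beginning is 1 − p^b, and the fraction who begin but are nonadherent on a given baseline day is p − p^b. This ignores withdrawal.

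For p = 0.4:
- Beginners: 0.2×0.6 + 0.6×0.936 + 0.2×0.9984 = 0.120 + 0.562 + 0.200 = 0.881
- Day 1: (0 + 0.6×0.336 + 0.2×0.3984)/0.881 = 0.281/0.881 = 32%
- Day 2: (0.120×0.2 + 0.281)/0.881 = 35%
- Days 4–5: (0.120×0.2 + 0.562×0.2 + 0.080)/0.881 = 25%
- Days 6–7: (0.562×0.2 + 0.080)/(0.562 + 0.200) = 25%
- Day 8 on: 20%

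For p = 0.3 the same steps give 24%, 27%, 22%, 23% and 20%. Applying the study-failure rule as well, by simulation, gives about the same values.

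**The case against.** Four objections have force.

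1. **The covariate list is open.** It is introduced by the word including, and the article condenses a fuller plan that may hold the term. A reader might infer that the plan rules out a period term; it does not. Even so, the list is specific down to the prior for study day and a caveat on day of week, while the one schedule-driven factor that the authors themselves discuss is not named.

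2. **An abstinence effect is not established.** A reader might infer that the model will show poor early adherence improving over time. The documents do not support that. They say only that abstaining may be a challenge for some, and give no size. The Discussion also cites rapid disengagement in app-based studies, which could offset or reverse such a pattern.

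3. **The size depends on who is modelled.** The text does not say whether the restriction to those who begin applies here. If it does, day-1 nonadherence in the 5-day arm is zero by definition, and the early excess shrinks and peaks on days 2–3.

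4. **The analysis is exploratory.** No hypothesis or power claim rests on it, and the term can be added at any time from recorded data. The authors also already warn that the abstinence baseline may not generalise.

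These limit the weight of the point. They do not remove it: the warning in the Discussion does not separate the two effects in the fitted curve.

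**Conclusion.** The point holds as a conditional one. As listed, the model has no term that separates abstinence days from treatment days, and baseline is tied to the early study days by design. Any difference in nonadherence between the two kinds of day would therefore be partly absorbed by the study-day curve.

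The size is illustrative. Under the assumed flat rates, with everyone modelled, the curve falls by one third (30% to 20%) or one half (40% to 20%) between day 1 and day 8. Restricted to those who begin, the fall from day 1 is about one sixth (24% to 20%) or a little over one third (32% to 20%), and it is not monotone. With no abstinence effect and everyone modelled, there is no artefact.

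Two stronger readings are not supported. The primary logistic regression on completion is not affected, since it has no study-day term. And the argument gives no reason to require separate terms for treatments A and B: it concerns abstinence against treatment, and both treatments contain caffeine.

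**What to change.** Add one time-varying indicator, baseline versus treatment period, taken from each participant's assigned schedule, to both the nonadherence rate and the withdrawal rate. State that the study-day curve is interpreted conditional on it. Separate A and B terms are optional.

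State also whether this model is restricted to participants who begin. That restriction lowers day-1 nonadherence by selection, and the indicator does not remove this. With 20% on all days and no abstinence effect, day 1 would be (0.6×0.192 + 0.2×0.2)/(0.2×0.8 + 0.6×0.992 + 0.2×1.0) = 0.155/0.955 = 16%.

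The cost is a sentence or two in the plan and one extra model term in each rate. The app already guides the treatment schedule and timestamps planned actions, so no new data are needed.
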